#### Satisfaction and safety

2.6.4

To evaluate the safety and satisfaction with the use of orthoses, a structured closed questionnaire will be applied consisting of 11 questions related to safety and seven related to satisfaction. Responses will be assessed using a 5-point Likert scale (1 = completely disagree; 2 = disagree; 3 = neither agree nor disagree; 4 = agree; 5 = completely agree). The questionnaire will be administered by phone one week after baseline and repeated at 3 and 6 months from baseline.

#### Comfort

2.6.5

To evaluate comfort when using the silicone orthoses, a visual numeric scale (where 0 corresponds to very uncomfortable and 10 corresponds to very comfortable when using the orthoses) will be applied.

#### Foot health and functionality

2.6.6

The Brazilian version of the Foot-Health Status Questionnaire [45] will be used. This instrument is divided into seven domains (pain, function, footwear, general health, physical activity, social capacity, and vitality) receiving a score of 0–100, where 100 represents the best condition and 0 represents the worst. The data will be tabulated in the Foot-Health Status Questionnaire software version 1.03.

#### Quality of life

2.6.7

The participants will fill out the Euro Quality of Life Instrument-5D (EQ-5D) questionnaire, which is a generic instrument for measuring health-related quality of life and allows for generating an index representing the value of an individual's health state [46]. The EQ-5D algorithm generates a value between −0.59 and 1.00, which represents the possible health status of a person (where 1 represents a perfect health value).

### Sample calculation and statistical analyses

2.7

The sample size calculation was performed using GPower v. 3.1 software [47] based on the primary outcome variable of the study: the presence of hyperkeratosis (pre-ulcerative lesions). For this outcome, the relative risk (RR) was calculated based on the incidence of hyperkeratosis after treatment with silicone digital orthoses in people with DPN from a previous study [35] using a contingency table. The sample size calculation used the following parameters: RR = 0.4913, test power = 0.80, α = 0.05, and a chi-squared test for contingency tables, resulting in a sample size of 54 participants. Assuming a 10 % loss to follow-up, 60 participants will be needed.

The inferential statistical analysis will be done by adopting an intention-to-treat approach. The imputation of missing values for the analyzed variables will be depend on the nature of the losses. After confirmation of normality (Kolmogorov–Smirnov test), homoscedasticity (Levene test), and imputation of means for missing data of variables with normal distribution, a two-way repeated measures ANOVA will be performed followed by Newman–Keuls post-hoc test to obtain group (CG and IG), time (baseline and 3 and 6 months), and group by time interaction effects. Significant differences will be considered with an alpha of 5 %. For the description of the intervention effect, the effect size (Cohen's d coefficient) and the difference between means with 95 % confidence intervals will be calculated.

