### Outcome assessments and timeline

2.5

Two researchers blinded to group allocation will perform the baseline and all follow-up assessments. IG participants will be assessed at baseline, after 7 days (via a telephone questionnaire about safety and comfort), at 3 months, and at 6 months. CG participants will be assessed at baseline and 3 and 6 months. Intervals of 3 and 6 months were established for the reassessments following the IWGDF guidelines, which recommend that individuals with DM classified as risk 2 need to be evaluated every 3–6 months and with risk 3 every 1–3 months. Table 1 presents the primary and secondary outcomes and the study period in which they will be evaluated according to the SPIRIT guidelines [40].

**Table 1 tbl1:** Primary and secondary outcomes of the study following the SPIRIT guidelines.

Outcomes		When participants will be assessed			
Primary	Measures	Baseline	7 days	3 m	6 m
Pre-ulcerative lesions and ulcers	Assessed according Colagiuri et al. (1995), which classifies hyperkeratosis into 6 grades.	**X**		**X**	**X**
**Secondary**	**Measures**				
Plantar pressure distribution during gait	Pressure peak, pressure-time integral, contact area by anatomical masking	**X**		**X**	**X**
Range of motion (ROM) of metatarsofalgeal joint	To assess ROM, a manual goniometer will be used to assess joint amplitude passively and actively	**X**		**X**	**X**
Toes alignment and flexibility	To measure toes alignment, toes will be photographed with markings on the metatarsophalangeal and interphalangeal joints.	**X**			**X**
Foot health and functionality	FHSQ-BR Domain scores	**X**		**X**	**X**
Quality of life	EQ-5D questionnaire	**X**		**X**	**X**
Satisfaction and safety	Satisfaction and Safety Questionnaires		**X**	**X**	**X**
Comfort	Analog numerical comfort scale		**X**	**X**	**X**

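### A relative risk of 0.4913 does not by itself determine the sample size of 54, so the stated 80% power is not established

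*Protocol article*

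**What the plan says.** Section 2.7 (Sample calculation and statistical analyses) bases the sample size on "the primary outcome variable of the study: the presence of hyperkeratosis (pre-ulcerative lesions". That is a yes/no outcome, and section 2.1 sets two arms with 1:1 allocation. The effect is described as a relative risk, obtained through a contingency table from the incidence in one earlier study. The inputs listed are "RR = 0.4913, test power = 0.80, α = 0.05, and a chi-squared test for contingency tables", "resulting in a sample size of 54 participants". A 10% loss then brings the total to 60. The software is G*Power 3.1.

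The section gives no risk for either arm, no Cohen's w and no df. Table 1 (section 2.5) describes the primary outcome measure as one "which classifies hyperkeratosis into 6 grades".

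**The concern.** The paragraph reads as a complete parameter list leading to a result, but the list does not lead there. The power of a chi-squared test on a contingency table depends on its df and on the noncentrality N × w². A relative risk supplies w only once a control risk is known. With the RR held at 0.4913, very different sample sizes all satisfy the printed inputs.

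The figure 54 also appears exactly if 0.4913 is treated as w with the df of a 2 × 6 table, which is not the table that a presence/absence outcome produces. That raises the possibility that one quantity was entered or labelled as another.

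This is the only power claim in the article. The Discussion says the trial should inform whether or not orthoses are adopted. How a null result should be read depends on whether the power was near 80%, well below it or well above it, and the plan as written does not settle that.

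**Working it through.** **Inputs from section 2.7:** effect 0.4913 (labelled RR), power 0.80, α = 0.05, chi-squared test for contingency tables, N = 54, 10% loss. **From section 2.1:** 1:1 allocation. **Assumed, because not given:** the control risk p₁, varied from 30% to 90%; a two-sided test without continuity correction.

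**Step 1. Dropout.** 54 / 0.9 = 60. This step is correct.

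**Step 2. Can 54 be reproduced with 0.4913 taken as w?** N = λ / w², rounded up, where λ is the noncentrality giving 80% power at α = 0.05, and w² = 0.4913² = 0.2414.

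| df | λ | λ / 0.2414 | N |
|---|---|---|---|
| 1 | 7.849 | 32.5 | 33 |
| 2 | 9.635 | 39.9 | 40 |
| 3 | 10.903 | 45.2 | 46 |
| 4 | 11.935 | 49.4 | 50 |
| 5 | 12.828 | 53.1 | **54** |
| 6 | 13.624 | 56.4 | 57 |

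At the stated 80% power, only df = 5 gives 54 (power 80.7% at N = 54, 79.9% at N = 53). Five df is a table of two groups by six categories: (2 − 1) × (6 − 1) = 5. Presence or absence in two groups has (2 − 1) × (2 − 1) = 1 df, and there w = 0.4913 needs 33.

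**Step 3. Take 0.4913 as a true RR.** With p₂ = 0.4913 × p₁ and p̄ = (p₁ + p₂) / 2, equal arms give w = (p₁ − p₂) / (2 × √(p̄(1 − p̄))). Power is that of the 1-df noncentral chi-squared with λ = 54 × w².

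Example at p₁ = 0.50: p₂ = 0.2457, p̄ = 0.3728, w = 0.2543 / (2 × 0.4836) = 0.263, λ = 54 × 0.263² ≈ 3.74, power 49%.

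| Assumed control risk | Orthosis risk | w | Power at N = 54 | N for 80% power |
|---|---|---|---|---|
| 30% | 14.7% | 0.183 | 27% | 235 |
| 50% | 24.6% | 0.263 | 49% | 114 |
| 60% | 29.5% | 0.307 | 62% | 84 |
| 70% | 34.4% | 0.356 | 75% | 62 |
| 75% | 36.8% | 0.384 | 81% | 54 |
| 80% | 39.3% | 0.415 | 86% | 46 |
| 90% | 44.2% | 0.487 | 95% | 34 |

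The printed inputs are therefore compatible with totals from 235 down to 34, a ratio of about 6.9, over this range.

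**Step 4. Other routes close to 54 with a true RR.** The section states neither sidedness nor continuity correction. A total within 2 of 54 arises at these control risks:
- about 0.72–0.75 for the two-sided uncorrected two-proportion formula;
- 0.73–0.76 for the 1-df chi-squared;
- 0.78–0.82 for two-sided with continuity correction;
- 0.64–0.68 for one-sided uncorrected;
- 0.71–0.75 for one-sided corrected.

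Each needs a control risk that the article does not print.

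**Step 5. Take 0.4913 as a true w for the 2 × 2 table.** λ = 54 × 0.2414 = 13.03, and power at 1 df is about 95%. (N = 54 is also the answer for w = 0.4913, 1 df and 95% power, but the section says 80%.)

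**The case against.** The best defence is that 54 may be right. The authors say they derived the RR from a contingency table, so they had both arm risks. If the control risk there was about 75%, a 1-df calculation gives 54. An article may condense, and leaving out the two risks alone would be a minor reporting gap. This stands as far as it goes: the documents cannot exclude that 54 is correct. It does not remove the point, because the paragraph presents its listed inputs as producing 54, and they do not.

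A reader might infer that 0.4913 was certainly typed in as w with 5 df. The documents do not support that. No df is printed, and the match was found by trying df values in turn. The link to six grades is also imperfect. The scale in section 2.6.1 starts at minimal thickening and has no callus-free class. Adding one would make a 2 × 7 table with 6 df and N = 57. The exact agreement at 5 df makes this a likely explanation, not a demonstrated one, and step 4 shows that other routes come close to 54.

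A reader might also infer that the trial is underpowered. That is not supported either. Nothing in the article fixes the control risk. The Introduction calls hyperkeratosis the most classic foot manifestation of neuropathy, and only IWGDF risk categories 2 and 3 are enrolled, so high control risks are at least plausible. If 0.4913 is a w, the error would have made the trial larger than needed for 80% power.

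**Conclusion.** The point holds in a limited form. The printed inputs do not determine 54, so 80% power is unestablished, and the direction of any error is unknown. If 0.4913 is a true RR, power with 54 evaluable lies between about 27% and 95% for control risks of 30% to 90%, and meets 80% from about 75% upward. If it is a true w on a 2 × 2 table, power is about 95%. The power figures assume 27 per arm, a two-sided 5% test and no continuity correction; the control risks are assumptions, not figures from the article. That an RR needs a control risk before it yields a sample size is a property of the test and rests on no outside source. That G*Power's contingency-table routine takes w is general knowledge of the software, and only the suggested explanation leans on it.

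**What to change.** Redo the calculation in section 2.7 as a comparison of two proportions (1 df). State the control and orthosis risks from the cited trial's contingency table, the resulting w, the df, the sidedness and whether a continuity correction is used. If 0.4913 was a w, relabel it and correct the df. Keep N = 60, and restate either the power with 54 evaluable or the detectable difference over a plausible range of control risks.

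The cost is one rewritten paragraph and a small table, from figures the authors say they already used. No further participants are needed. The drawback is that the restated power may be less favourable than 80%.

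### Single mean imputation is fixed for normally distributed outcomes without saying which mean: depending on the choice, it understates standard errors or pulls the group difference towards zero

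*Protocol article*

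**What the plan says.** Section 2.7 of the protocol article adopts an intention-to-treat analysis and opens its account of missing data with a general principle: "The imputation of missing values for the analyzed variables will be depend on the nature of the losses". No rule follows that links a type of loss to a method. The next sentence names one method, "imputation of means for missing data of variables with normal distribution", and lists it with the normality and variance checks as a step before the model. Then "a two-way repeated measures ANOVA will be performed followed by Newman–Keuls post-hoc test" tests group, "time (baseline and 3 and 6 months), and group by time interaction effects", at a 5% level. Cohen's d and mean differences with 95% confidence intervals are to be reported as well.

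The text does not say whether the mean is that of the arm at the visit, of both arms at the visit, or of the participant over time. It describes no correction for having imputed. The planned loss is 10%: the calculation gives 54 participants, and after "loss to follow-up, 60 participants will be needed". Section 2.4.2 adds that an intervention participant who gives up the orthoses without explanation leaves the study and counts as a drop-out.

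**The concern.** A mean put in place of a missing value is then analysed as if it had been measured. It adds to the sample size and the degrees of freedom but contributes little or no variation, so the analysis credits itself with information that it does not have. What this does to the results depends on which mean is used, and the plan leaves that open. Intervals may be too narrow and p values too small, or the estimated effect may be diluted. An open choice can also be settled after the data have been seen.

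At stake are the p values, effect sizes and confidence intervals of any continuous outcome that passes the normality check and has missing follow-up. Candidates are plantar pressure, range of motion and the questionnaire scores, all secondary outcomes in section 2.6.

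**Working it through.** **Inputs from section 2.7.** N = 60 at 1:1 (ratio from section 2.1), so 30 per arm; 10% loss; α = 0.05, taken as two-sided because sidedness is not stated; 2 groups by 3 times.

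**Assumptions.** Losses are completely at random and equal between arms unless stated. Within-participant correlation is not given in the article; 0.3 to 0.8 with compound symmetry was used.

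**The plan's own figure.** 54 / (1 − 0.10) = 60, which matches. It leaves 27 observed and 3 missing per arm.

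**1. Arm-by-visit mean.** The arm means do not change, so the estimated difference and its true variability do not change either. Only the calculated standard error does. With n per arm and m missing:

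SE ratio = √[ ((n − m − 1)/(n − 1)) × ((n − m)/n) ]

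- n = 30, m = 3: √[(26/29) × (27/30)] = 0.898
- n = 30, m = 6: √[(23/29) × (24/30)] = 0.797

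The analyst uses the critical value for 58 degrees of freedom, 2.002, but the valid statistic has 52 (m = 3) or 46 (m = 6):

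- m = 3: P(|t₅₂| > 2.002 × 0.898 = 1.798) = 7.8%
- m = 6: P(|t₄₆| > 2.002 × 0.797 = 1.594) = 11.8%

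Simulation of the 6-month contrast (100,000 runs, 3 missing per arm, SD = 1):

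| Method | Mean SE | True SD of estimate | Type I error | Coverage, no true difference | Estimate when truth is 0.80 | Coverage when truth is 0.80 |
|---|---|---|---|---|---|---|
| Observed data only | 0.271 | 0.273 | 5.0% | 95.0% | 0.80 | 95.0% |
| Arm-by-visit mean | 0.243 | 0.273 | 7.9% | 92.1% | 0.80 | 92.2% |
| Pooled visit mean | 0.244 | 0.245 | 5.0% | 95.0% | 0.72 | 93.8% |

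**2. The planned 2 × 3 ANOVA with arm-by-visit means.** Simulation at 10% loss (20,000 runs per setting) gives 5.7 to 6.2% for the group, time and interaction tests if only month 6 is missing, and 6.7 to 7.5% if months 3 and 6 are both missing. Restricting the ANOVA to complete participants gives 4.9 to 5.3%.

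**3. Pooled visit mean.** Each arm's mean is a mix of 90% observed data and 10% common value, so the difference becomes 0.90 × 0.80 = 0.72 SD. Between-arm tests stay at 4.8 to 5.3%, because the estimate and its standard error shrink together. The time test rises to 5.9 to 7.5%.

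**4. Participant's own mean.** All tests stay at 4.8 to 5.3%. The value put in at follow-up comes from earlier visits, however. With no difference at baseline:

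- If 10% miss both follow-ups, they receive their baseline value: 0.90 × 0.80 + 0.10 × 0 = 0.72.
- If 10% miss month 6 only and the difference at month 3 is also 0.80, they receive the average of baseline and month 3: 0.90 × 0.80 + 0.10 × 0.40 = 0.76.

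**5. Unequal loss.** If all 6 losses fall in the intervention arm, still at random, type I error is 7.9% with arm means and 4.8% with pooled means. None of these runs covers losses related to the outcome.

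**The case against.** The strongest objection is that the article does not commit to arm means. A reader might infer that the 5% level is exceeded whichever mean is used. The text does not support that: with pooled or participant means the between-arm tests hold their level. The 7.8% belongs to a single-visit contrast, whereas the planned ANOVA is milder, and the 11.8% needs twice the planned loss. All of this stands.

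Other tempting readings also go too far:

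- **That normality is the only trigger for imputation.** The sentence just before ties imputation to why data are lost. It gives no rule, but the principle is there, and normality then limits which variables receive a mean.
- **That the primary outcome is left without any handling.** A condensed article commonly leaves detail by outcome to the full protocol or analysis plan, which are not shown.
- **That every continuous result is wrong, or that the intention-to-treat analysis is invalid.** The rule reaches only normally distributed variables with missing values. Bounded scores such as the foot-health domains or EQ-5D may not qualify.

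What does not stand is the idea that an unnamed mean makes the problem go away. Arm means overstate precision, and the other two choices dilute a real effect in the cases worked above. Nor is this a detail left for later: the article names the method and places it ahead of its only named inferential analysis.

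**Conclusion.** The point holds in conditional form. Section 2.7 fixes single mean imputation for normally distributed variables, does not say which mean, and allows nothing for imputation uncertainty. At the planned 10% loss:

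- **Arm-by-visit means:** 6-month standard error about 0.90 of its correct size, error about 7.8% and coverage about 92% for that contrast; about 6 to 7.5% error in the planned ANOVA.
- **Pooled visit means:** between-arm error near 5%, but the difference shrinks by about 10% (0.80 to 0.72 SD) and coverage falls to about 94%.
- **Participant means:** error near 5%, with earlier values standing in for follow-up.

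The effect is moderate and bears mainly on secondary outcomes. These sizes assume losses completely at random, compound symmetry and a two-sided test. The drop-out rule in section 2.4.2 applies to the intervention arm, so actual losses may be related to arm and to tolerance of the device. The figures do not include any bias from that.

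**What to change.** In section 2.7, delete mean imputation. Analyse the continuous outcomes with a likelihood-based mixed model for repeated measures, with group, time and their interaction, on all randomised participants who have any data. This uses the observed values as they are and is valid if data are missing at random. It also removes the need to choose a mean.

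Add a prespecified sensitivity analysis for departures from missing at random, because unexplained stopping of the orthoses takes participants out of the intervention arm only. Keep the sentence about the nature of the losses only if it is completed with a rule saying what will be done in which case.

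The cost is a few lines of text, standard software, a little more analysis work, and confidence intervals slightly wider than mean imputation would have shown. The article reports that recruitment is under way, so the change should be made before the data are analysed.

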**Methods:**

In this superiority randomized controlled parallel trial with single-blind assessment, 60 participants will be allocated to the control group (CG) or the intervention group (IG). The CG will receive specialized nurse-administered foot care, including callus removal, nail care guidance, and self-care education. The IG will receive the same care plus a customized silicone orthosis for toe realignment for 6 months. Assessments will occur at baseline and 3 and 6 months for the primary outcomes (pre-ulcerative lesions and ulcer incidence) and secondary outcomes (pressure distribution, foot function and health, quality of life, safety, and comfort). Two-way ANOVAs (p < .05) will assess group, time, and group by time effects following an intention-to-treat approach.

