### Primary and secondary outcomes

2.6

The incidence of ulcers and pre-ulcerative lesions will be considered the primary outcomes. The plantar pressure distribution during walking, metatarsophalangeal joint range of motion (ROM), toe alignment, foot function, overall foot health, quality of life, satisfaction, safety, and comfort will be secondary outcomes.

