**Fig. 4 fig4:**
[figure not shown]
Grades 1 to 6 of severity of pre-ulcerative lesions and ulcers.

Grades 1 to 4 refer to pre-ulcerative lesions, while Grades 5 and 6 are already established ulcers. If the participant is classified as Grade 5 or 6 at baseline assessment, they will not be included in the study but may be included later after the ulcer has healed.

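### The primary outcome is an incidence sized with a chi-squared test and a relative risk, but the only analysis named is a normality-gated repeated-measures ANOVA, with no alternative for data that fail the gate

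*Protocol article*

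**What the plan says.** All references are to the protocol article.

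- **Outcome.** Section 2.6: "The incidence of ulcers and pre-ulcerative lesions will be considered the primary outcomes". Section 2.6.1 and Table 1 measure this on a six-grade scale, on which "Grades 1 to 4 refer to pre-ulcerative lesions, while Grades 5 and 6 are already established ulcers".
- **Sizing.** Section 2.7 names presence of hyperkeratosis as the primary variable. The inputs are "RR = 0.4913, test power = 0.80, α = 0.05" and "a chi-squared test for contingency tables, resulting in a sample size of 54 participants", raised to 60 for 10% loss. The relative risk comes from an earlier study; the control-group risk is not given.
- **Analysis.** In section 2.7, after Kolmogorov–Smirnov and Levene checks, "a two-way repeated measures ANOVA will be performed", with Newman–Keuls post-hoc tests. For the effect, "the effect size (Cohen's d coefficient) and the difference between means with 95 % confidence intervals will be calculated".
- **Abstract.** After listing the primary outcomes it says: "Two-way ANOVAs (p < .05) will assess group, time, and group by time effects following an intention-to-treat approach".

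The article names no test of proportions, no relative risk as a reported result, no binary or ordinal model, and no method for variables that fail the checks.

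**The concern.** The trial is sized for one comparison and commits itself to another. The objective is prevention of lesions and ulcers, and the sample size rests on the ratio of two proportions. The named analysis compares means of a variable that must first look normal.

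If the outcome is coded present/absent, the plan's own condition rules out the plan's only method. If the ordinal grade is analysed instead, the result does not answer the question on which the trial was sized. Either way the primary comparison is not fixed in advance. Choosing a test after the normality check has failed is a data-dependent choice of primary analysis, which prespecification is meant to prevent.

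This goes beyond detail left to an analysis plan. The article states a method, a gate and an effect measure, in both abstract and body, and they do not fit the primary outcome. An unseen plan with a binary analysis would contradict the published text.

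**Working it through.** **1. The plan's own figures**

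Inflation for loss: 54 / (1 − 0.10) = 60, which reproduces.

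The 54 does not follow uniquely, because a relative risk without a control risk does not fix N. With p₁ the control risk, p₂ = 0.4913 × p₁ and p̄ their mean, the two-sided uncorrected formula per arm is

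n = [1.96·√(2p̄(1−p̄)) + 0.842·√(p₁(1−p₁) + p₂(1−p₂))]² / (p₁−p₂)²

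| Assumed control risk | p₂ | Total N for 80% power | Power with 27 per arm |
|---|---|---|---|
| 50% | 24.6% | 112 | 0.49 |
| 60% | 29.5% | 82 | 0.62 |
| 70% | 34.4% | 60 | 0.76 |
| 75% | 36.8% | 52 | 0.83 |
| 80% | 39.3% | 44 | 0.88 |

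Total N is 54 at a control risk of about 74%. That is not the only route. With a continuity correction, 54 arises at about 80%. Entering 0.4913 directly as effect size w gives 54 with 5 degrees of freedom, but 33 with the 1 degree of freedom of a 2×2 table. The control risk therefore cannot be inferred from the 54.

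**2. Can a 0/1 outcome pass the normality check?**

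For a variable that is 1 with probability p, with SD s = √(p(1−p)), compare its step distribution function with the normal of the same mean and SD. The distance is smallest at p = 0.5, where s = 0.5. Just below 0 the normal function is Φ(−1) = 0.159, and at 0 the step function rises to 0.5. So

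D = 0.5 − 0.159 = 0.341.

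Elsewhere it is larger: 0.408 at p = 0.37 and 0.468 at p = 0.25 or 0.75.

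The 5% critical values of the Kolmogorov–Smirnov test are 0.254 (n = 27), 0.242 (n = 30), 0.181 (n = 54) and 0.172 (n = 60). The minimum distance exceeds all of them, so a presence/absence outcome fails at every prevalence, by group or pooled. This takes the check as applied to the outcome itself, as section 2.7 reads.

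**3. What ANOVA on the grades would estimate**

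Whether the grades pass the gate depends on their distribution, which the article does not give. As an assumed example, spread people evenly over five levels coded 0 to 4 (mean 2, SD √2 = 1.414). At level 1 the step function is 0.4 and the normal is Φ(−0.707) = 0.240. So D = 0.160, below 0.242. The grades might pass.

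Passing does not repair the estimand. A mean-grade difference counts a step from Grade 1 to 2 (more thickening) the same as one from Grade 4 to 5 (an ulcer appears). The scale in section 2.6.1 also starts at minimal thickening, so the score of a foot without hyperkeratosis is not defined. The result is neither an incidence nor the relative risk of 0.4913.

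**The case against.** The strongest reply is that ANOVA need not be useless here, and parts of that reply stand.

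- **A reader might infer that ANOVA cannot yield a risk difference.** That is wrong. For 0/1 data the difference between means is the risk difference, and section 2.7 plans mean differences with 95% intervals. With assumed counts of 20/27 v 10/27, the difference is 0.741 − 0.370 = 0.37 either way. The pooled-t interval is 0.11 to 0.63 and the Wald interval 0.12 to 0.62. But the plan does not propose this use, and its normality gate bars it.
- **A reader might infer that the relative risk can never be reported.** Grades are recorded at baseline, 3 and 6 months (Table 1), so it stays computable. The fault is that it is not prespecified.
- **A reader might infer that the grades would also fail the gate almost surely.** The documents do not support that (step 3 of the working). Only the 0/1 coding is certain to fail.
- **A reader might object that the group main effect averages in the baseline.** It does, but the plan also includes the group-by-time interaction, and nothing makes the main effect the deciding test.
- **The gate could be read as limiting ANOVA to normally distributed variables, leaving the rest to an unseen plan.** The abstract weakens this reading: it lists the primary outcomes and then names ANOVAs without qualification.

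None of these supplies an analysis of incidence or removes the conflict with the sizing.

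**Conclusion.** The concern holds. The analysis named does not match the outcome and test on which the trial was sized, and there is no method for data that fail the stated check. For a presence/absence outcome failure is certain (0.341 or more against about 0.24 at n = 30). For the grades, ANOVA answers a different question.

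The harm is to the estimand and its prespecification. A reader might infer a large loss of power; the documents do not support that. Under assumed risks of 74.5% v 36.6% (0.745 × 0.4913 = 0.366), 27 per arm, a latent correlation of 0.5 and baseline prevalence of 50–90%, simulated power was 73–86% for ANOVA on 0/1 data and 81–82% for chi-squared. Those risks are not in the article. Over assumed control risks of 50–80%, chi-squared power alone runs from 0.49 to 0.88, so any power comparison rests on an assumption.

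Since this governs the trial's main conclusion, it should be corrected before the outcome data are examined. Section 3.1 reports that recruitment is under way.

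**What to change.** In section 2.7 and the abstract:

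1. Name one binary primary analysis, of hyperkeratosis as sized.
2. Define an incident lesion. Only Grades 5 and 6 are excluded at entry, so participants may enter with calluses. State how lesions present at baseline are counted, and how a lesion seen at 3 months but not at 6 is counted. A simple 6-month proportion would be a point prevalence, not the incidence named in section 2.6.
3. Compare the groups by a chi-squared/Cochran–Mantel–Haenszel test stratified by IWGDF risk category, which section 2.3 already uses as a stratum. Alternatively, use modified-Poisson regression adjusted for that stratum, and for baseline lesion status if participants with lesions are counted. Do not also stratify the Cochran–Mantel–Haenszel test by baseline grade: with 54 to 60 people the cells would be sparse.
4. Report the relative risk and the risk difference with 95% confidence intervals.
5. Report ulcers (Grades 5 and 6) separately, and keep ANOVA for the continuous secondary outcomes.

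Ordinal or longitudinal binary models are optional supportive analyses. The cost is rewording and slightly more analysis work; no new data are needed.
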